## Abstract

**Background:**

Delirium is a serious and distressing neuropsychiatric condition, which is prevalent across all palliative care settings. Hypoactive delirium is particularly common, but difficult to recognize, partly due to overlapping symptoms with depression and dementia. Delirium screening tools can lead to earlier identification and hence better management of patients. The 4AT (4 ‘A’s Test) is a brief tool for delirium detection, designed for use in clinical practice. It has been validated in 17 studies in over 3,700 patients. The test is currently used in specialist palliative care units, but has not been validated in this setting. The aim of the study is to determine the diagnostic accuracy of the 4AT for delirium detection against a reference standard, in hospice inpatients.

**Methods:**

240 participants will be recruited from the inpatient units of two hospices in Scotland. If a patient lacks capacity to consent, agreement will be sought from a legal proxy. Each participant will complete the 4AT and a reference standard assessment based on the diagnostic delirium criteria in the fifth edition of the Diagnostic and Statistical Manual of Mental Disorders (DSM-5). This will be supplemented by tests of cognition and attention, including reverse days of the week, counting down from 20 to 1, Vigilance 'A', the Observational Scale for Level of Arousal, the modified Richmond Agitation Sedation Scale and the Delirium Rating Scale-Revised-98. The assessments will be conducted in a randomized order by two independent clinicians, who will be blinded to the results until both are complete. Primary outcomes will be the sensitivity and specificity of the 4AT in detecting delirium.

**Discussion:**

The findings will inform clinical practice regarding delirium assessment in palliative care settings.

**Trial registration:**

ISRCTN ISRCTN97417474 (21/02/2020).

## Abbreviations

DSM-5Diagnostic and Statistical Manual of Mental Disorders, 5^th^ editionDSM-IVDiagnostic and Statistical Manual of Mental Disorders, 4^th^ editionDSM-IIIDiagnostic and Statistical Manual of Mental Disorders, 3^rd^ edition, RevisedCAMConfusion Assessment MethodbCAMBrief Confusion Assessment Method4AT4 ‘A’s testSQiDSingle Question in DeliriumNuDESCNursing Delirium Screening ScaleDOSDelirium Observation ScaleDRSDelirium Rating ScaleDRS-R-98Delirium Rating Scale Revised 98MDASMemorial Delirium Assessment ScaleAMT-4Abbreviated Mental Test -4CCCConcordance Correlation CoefficientACCORDAcademic and Clinical Central Office for Research and Development

## Background

Delirium is a serious and distressing neuropsychiatric condition, characterized by an acute disturbance in attention, awareness and cognition. Delirium severity may fluctuate throughout the day, and be associated with disturbances in the sleep-wake cycle. Cognitive changes may impact memory, orientation, language, visuospatial ability and perception^1^. Delirium can be highly distressing for patients and their families and is associated with poor outcomes^2–6^.

Delirium is extremely common across all palliative care settings^7,8^. A recent systematic review estimated the median (range) point prevalence of delirium on admission to palliative care inpatient settings as 32% (6.6%–73%) and period prevalence prior to death as 75% (58%–88%)^7^. Hypoactive delirium is more common than other subtypes in palliative care^9–11^ but may be less noticeable and go under-recognised due to overlapping symptoms with depression, dementia and fatigue^11–13^.

International guidance recommends routine assessment for risk factors of delirium on admission to hospital and other care settings, and subsequently if there are any fluctuations or changes in behaviour or cognition^14–18^. Delirium assessment tools are recommended and may lead to earlier detection. Improved detection may lead to better management, including investigation and treatment of the underlying cause and/or better symptom control, resulting in more favourable outcomes for both patients and their families.

Delirium tools are available for different purposes^19^: for delirium detection at first presentation, and at other times when delirium is first suspected: the Confusion Assessment Method (CAM)^20^, shorter versions, including the brief Confusion Assessment Method (bCAM)^21^, the 4 ‘A’s test (4AT)^22^ and informant screening tools, such as the Single Question in Delirium (SQiD)^23^.for monitoring of new onset delirium in inpatients, on a regular basis, daily or more frequently: the Nursing Delirium Screening Scale (NuDESC)^24^ and Delirium Observation Scale (DOS)^25^.as research assessments: The Delirium Rating Scale (DRS) and the Delirium Rating Scale Revised-98 (DRS-R-98)^26^.

Table 1 shows examples of validation studies in palliative care and oncology populations.

The DRS-R-98, a clinician-rated 16-item scale with 3 diagnostic and 13 severity scales, is able to distinguish reliably from depression and dementia^26^. Use in clinical practice is limited because of training required prior to use and time taken to administer (at least 20–30 minutes with the patient, plus additional time to gather informant history and review case notes)^11,27^.

The Memorial Delirium Assessment Scale (MDAS), a 10-item scale, used for delirium detection and severity monitoring, takes approximately 10 minutes with the patient, plus additional time to gather informant history^30^. It has a simpler format and is easier to rate than the DRS-R-98, but still requires moderate training to administe^r27^. A study in a palliative care inpatient unit demonstrated 97% sensitivity and 95% specificity (cutoff score = 7)^31^.

The CAM and its shorter variants are quicker to administer than either the MDAS or DRS-R-98 (approximately 5–10 minutes), but still require moderate training prior to use, as well as additional cognitive testing^27^. Aspects requiring subjective judgement by the assessor can be more complex and time-consuming to rate, plus there is limited advice for scoring non-verbalizing patients^39^. This may account for high levels of sensitivity and specificity in some studies^33,34^, but lower results when scored by those less experienced^23,33^.

The informant tool, the Single Question in Delirium (SQiD), which asks ‘Do you feel that (patient’s name) has been more confused lately?’, has been validated in oncology patients (80% sensitivity and 71% specificity), but not in palliative care patients^23^. Use of the SQiD is limited when an informant is unavailable.

The 4‘A’s Test (4AT) is a short bedside test for detecting delirium, for use in clinical practice^22^. It takes a few minutes to complete and incorporates 4 items: (1.) An observational measure of alertness, (2.) The Abbreviated Mental Test-4 (AMT4), (3.) The Months of the Year Backwards test, and (4.) Evidence of significant change or fluctuation in alertness, cognition or other mental function arising over the last 2 weeks and still evident in the last 24 hours. The first 3 items are assessed at the patient’s bedside. The last item is derived directly by the assessor or from informant history (i.e. taken from case notes, clinical staff or a relative or carer). The 4AT can be used by any healthcare professional, either at first contact or when delirium is suspected. It is one of the most frequently validated delirium tools in the literature. A recent systematic review and meta-analysis of 17 studies involving 3702 older adults in medicine, surgery, emergency and care home settings, demonstrated a pooled sensitivity of 88% and pooled specificity of 88%^40^. The 4AT’s advantages over other tools are that no special training is required prior to use, and it is quick and easy to administer. Furthermore, all patients can be assessed, including those unable to communicate (patients with severe drowsiness or agitation.)

The 4AT is recommended for identifying patients with delirium^14^, and is currently used in palliative care settings^41–43^, but has not been validated for delirium screening in a terminally ill population.

## Study objective

The study objective is to determine whether the 4AT is a valid tool for delirium detection in specialist palliative care settings. The diagnostic accuracy of the 4AT will be compared against a reference standard delirium assessment, based on the diagnostic criteria of the fifth edition of the Diagnostic and Statistical Manual of Mental Disorders (DSM-5) (Table 2)^1^.

## Methods

### Study overview

In developing this protocol, we drew on the study design and procedures of a previous 4AT validation study conducted in emergency departments and acute medical wards^39^. This study is a prospective diagnostic accuracy study of the 4AT in a representative sample of hospice inpatients. Each participant will independently complete the 4AT and the reference standard delirium assessment based on DSM-5 criteria. Study procedures are described in Figure 1.

### Setting

The study will take place at two hospices in Scotland. The hospices have 17 and 24 inpatient beds, respectively, and admitted a combined total of 700 patients in 2019. Patients with advanced progressive or incurable disease are admitted for complex end of life care, or because they have uncontrolled pain and/or other complex physical or psychological issues, that cannot be managed in other care settings.

### Participants and sample size

Participants admitted acutely to the hospices will be included if they are aged 18 years or over. Patients will be excluded if they are comatosed, unable to communicate in English, are severely dysphasic or have a combined severe hearing and visual impairment, which would limit participation in the study’s tests. Patients will also be excluded if there is a high level of patient and family distress, as judged by the clinical team, or the patient has an acute life-threatening illness requiring time-critical intervention (e.g. suspected spinal cord compression).

A recent meta-analysis of 17 studies on the diagnostic accuracy of the 4AT in a variety of clinical settings, reported a pooled sensitivity of 0.88 (95% CI 0.80-0.93) and a pooled specificity of 0.88 (95% CI 0.82-0.92)^40^. In line with guidance described by Flahault *et al.* (2005)^44^ which suggests a sample size of 176, given a sensitivity/specificity of 0.85, and a minimal acceptable lower confidence level of 0.75, we plan to recruit 240 patients from the inpatient units across both hospices. We estimate that 80% of those recruited will complete the assessments, allowing data analysis on at least 200, slightly above the 176 needed.

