### Data analysis

The diagnostic test accuracy of the 4AT for delirium detection in specialist palliative care inpatient populations, versus the reference standard, will be determined using sensitivity, specificity, and positive and negative predictive values. The exact binomial 95% confidence interval will be reported for each measure. A ROC curve analysis will be performed, and the area under the ROC curve and its 95% confidence interval will be reported. Analyses will be completed using IBM SPSS Statistics.

Participants with missing data from the 4AT and reference standard assessments will be included in the statistical analysis, if there is enough information to decide on categorisation. Cases with insufficient information will be excluded, and expert panel advice will be sought where there is uncertainty.

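### The 176 patients called for reproduce only as the size of one reference group, but the plan sets the figure against the whole sample, so precision is weaker than implied, mainly for sensitivity

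*Protocol article*

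**What the plan says.** The Abstract (Methods) of the protocol article names two primary outcomes, the sensitivity and the specificity of the 4AT. Under Participants and sample size, the size is taken from cited guidance, "which suggests a sample size of 176, given a sensitivity/specificity of 0.85, and a minimal acceptable lower confidence level of 0.75". The plan continues: "we plan to recruit 240 patients from the inpatient units across both hospices". It closes: "We estimate that 80% of those recruited will complete the assessments, allowing data analysis on at least 200, slightly above the 176 needed". So 176 is set against the total number analysed. Neither prevalence nor a split into patients with and without delirium enters the calculation.

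Prevalence appears only in the Background, where a review is cited for a "median (range) point prevalence of delirium on admission to palliative care inpatient settings as 32% (6.6%–73" (that is, 6.6% to 73%). Under Data analysis, "The exact binomial 95% confidence interval will be reported for each measure".

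**The concern.** Sensitivity is a proportion among patients with delirium, and specificity a proportion among those without. Each has its own denominator, and the two denominators add up to the number analysed. If 176 is the denominator needed to bring the lower limit of one such proportion to 0.75, a total a little above 176 cannot supply it for both. The document would then be telling its readers that the size is adequate for two primary outcomes when it is not adequate in the sense stated. The outcome with the smaller group suffers most. At the cited median prevalence that is sensitivity, the measure that bears on missed delirium, which the Background and Discussion give as a main reason for the study.

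**Working it through.** **Inputs.** Planning value 0.85, lower limit 0.75, stated size 176, recruitment 240 and completion 80% (Participants and sample size); prevalence median 32%, range 6.6% to 73% (Background); exact binomial 95% intervals (Data analysis). The 50% prevalence is mine, as the most favourable case for two equal groups.

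**Step 1: reproduce 176.** For a single proportion with n patients, let c be the smallest count whose exact (Clopper-Pearson) lower limit is at least 0.75. The assurance is P(X ≥ c), with X binomial(n, 0.85).

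- One-sided 95% limit: at n = 176, c = 142 and the assurance is 0.952; at n = 175 it is 0.934. The smallest n reaching 0.95 is exactly 176.
- Two-sided 95% interval: the smallest n reaching 0.90 is 174; at n = 176 the assurance is 0.899.

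The article states neither convention; both are reconstructions. Each is the size of one group, and prevalence plays no part in either. As a check on a total-sample reading, a simple precision formula (half-width 0.10) gives 1.96² × 0.85 × 0.15 / 0.10² = 49 patients with delirium. Divided by prevalence, that is 49/0.32 ≈ 154 at 32% and 49/0.50 = 98 at 50%. It would take a prevalence of about 28%, which the article does not give, to arrive at 176.

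**Step 2: total needed for 176 in each group.** N = max(176/π, 176/(1 − π)), with π the prevalence.

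- π = 50%: 176/0.50 = 352, the minimum over all prevalences
- π = 32%: 176/0.32 = 550
- π = 73%: 176/0.27 = 652
- π = 6.6%: 176/0.066 = 2,667

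**Step 3: number analysed.** 240 × 0.80 = 192. To analyse 200 at 80% completion, 200/0.80 = 250 would have to be recruited. Both 192 and 200 exceed 176 and fall well short of 352.

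**Step 4: what 192 delivers if the true value is 0.85.** Group sizes are 192π and 192(1 − π), rounded, with every patient classed as with or without delirium. The interval is the exact two-sided 95% interval at the count nearest to 0.85n. The last column is the chance that its lower limit is at least 0.75.

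| Prevalence | Outcome | n | Expected result | Exact 95% CI | Chance |
|---|---|---|---|---|---|
| 32% | Sensitivity | 61 | 52/61 | 0.738–0.930 | 0.42 |
| 32% | Specificity | 131 | 111/131 | 0.774–0.904 | 0.76 |
| 50% | Each | 96 | 82/96 | 0.767–0.918 | 0.635 |
| 73% | Sensitivity | 140 | 119/140 | 0.780–0.905 | 0.80 |
| 73% | Specificity | 52 | 44/52 | 0.719–0.931 | 0.32 |
| 6.6% | Sensitivity | 13 | 11/13 | 0.546–0.981 | 0.12 |
| 6.6% | Specificity | 179 | 152/179 | 0.788–0.898 | 0.92 |

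With a one-sided 95% limit, the chances at 32% prevalence are 0.57 for sensitivity and 0.88 for specificity, against the 0.95 that this convention gives at n = 176.

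**Step 5: stability.** Exact binomial chances saw-tooth with n: the two-sided figure is 0.42 at n = 61, 0.36 at 64 and 0.48 at 65. For specificity it is 0.76 at 131 and 0.82 at 132. They are best read as roughly 0.4 and 0.75 to 0.8. If true sensitivity is 0.88, the pooled value cited in the same paragraph, the chance at n = 61 is 0.69 two-sided or 0.81 one-sided.

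**The case against.** Four points against a stronger reading have force.

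- **The convention is inferred.** The article gives 176, 0.85, 0.75 and a citation, but no sidedness and no assurance probability. A reader might infer that 176 belongs to a one-sided limit and so clashes with the intervals planned under Data analysis. The document does not support that: a two-sided 95% interval with 90% assurance gives 174, almost the same number.
- **There is no success rule.** A reader might infer that the study is likely to fail its own criterion. The 0.75 appears only as a sample-size input, and the analysis section describes estimation with intervals and sets no threshold to pass.
- **The probabilities depend on assumptions.** The 32% is a literature median and not a planning value. That the sensitivity interval will more likely than not extend below 0.75 holds at a true value of 0.85 and a prevalence near 32%. It does not hold at 50% prevalence (0.635), nor at a true sensitivity of 0.88 with 61 cases (0.69).
- **The shortfall is uneven.** At 32% prevalence it is large for sensitivity and modest for specificity. At 6.6% the group without delirium alone passes 176.

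These points limit how strongly the consequence can be put. None of them rescues the comparison of 176 with the total, because at no prevalence do 192 or 200 patients contain two groups of 176. Nor is this a detail left to a fuller document: the article makes a positive statement of adequacy, and that statement is wrong as written.

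**Conclusion.** The point holds in this form: 176 reproduces as a one-group size, the plan applies it to the whole sample, and the lower limit of 0.75 therefore does not have the implied assurance for both primary outcomes. The requirement for both groups is at least 352 analysable patients against 192 expected. This part depends on no prevalence assumption; it rests only on reading 176 as a one-group size, the only reading that reproduces it at a documented prevalence.

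The size of the loss does depend on assumptions. At 32% prevalence and true values of 0.85, sensitivity would be reported with an interval of about 0.74 to 0.93, and specificity with about 0.77 to 0.90. At high prevalence specificity becomes the less precise outcome. If patients categorised under Table 4 as possible delirium or undetermined were left out of both groups, the groups would be smaller still. The consequence is less precision than the plan implies, not a predicted failure of the study. The number analysed is also misstated, as 80% of 240 is 192; that slip alone would not matter, since 192 still exceeds 176.

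**What to change.** Keep 240. In Participants and sample size:

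1. Delete the statement that 176 in total is needed and met.
2. Correct the expected number analysed to 192.
3. State the expected group sizes and exact 95% intervals for sensitivity and specificity at several prevalences, for example 32%, 50% and 73%, taken from the table above. Label prevalence as an assumption, and likewise the probability convention behind 176 if that number is kept for reference.
4. Say which outcome will be the less precise at each prevalence.

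Possible wording: With 192 analysable patients and an assumed prevalence of 32%, about 61 will have delirium and 131 will not. If true sensitivity and specificity are 0.85, the expected exact 95% confidence intervals are about 0.74 to 0.93 and 0.77 to 0.90.

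Interval widths serve better here than probabilities of clearing 0.75, which shift noticeably when a group gains or loses one patient.

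The cost is one rewritten paragraph, with no change to recruitment, conduct or analysis. The drawback is that the stated precision becomes less favourable.

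### The analysable number is wrong as written: 80% of 240 recruited is 192, not a minimum of 200

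*Protocol article*

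**What the plan says.** The section Participants and sample size of the protocol article sets out the calculation in three steps.

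- **Requirement.** It relies on published guidance "which suggests a sample size of 176, given a sensitivity/specificity of 0.85, and a minimal acceptable lower confidence level of 0.75".
- **Recruitment.** It then says "we plan to recruit 240 patients from the inpatient units across both hospices". The abstract gives the same total: "240 participants will be recruited from the inpatient units of two hospices in Scotland".
- **Yield.** It closes with the completion assumption and the result drawn from it: "We estimate that 80% of those recruited will complete the assessments, allowing data analysis on at least 200, slightly above the 176 needed".

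The Data analysis section bears on who is finally analysed. Participants with missing data are kept if they can still be categorised. Otherwise, "Cases with insufficient information will be excluded, and expert panel advice will be sought where there is uncertainty".

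**The concern.** The analysable number is presented as following from two stated inputs, and it does not follow from them. It is also worded as a minimum, whereas a product of recruitment and an estimated completion rate is an expected value that the study may fall below.

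This sentence is the article's only statement of how many patients will be analysed, and its only statement of the reserve over the requirement. Any later precision statement or recruitment monitoring that started from 200 would start from a number that the plan's own assumptions do not support. Recruitment was paused in March 2020 and is due to resume, so the true reserve is a figure the team may need.

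**Working it through.** **Inputs**, all from Participants and sample size: recruited N = 240; completion rate c = 0.80; requirement 176; stated analysable number 200 or more.

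**1. Try to reproduce the stated figure.** Expected completers = N × c = 240 × 0.80 = 192. The stated 200 is not reproduced. The gap is 200 − 192 = 8, which is 8/192 = 4.2% of the correct figure.

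**2. What 200 would require.**
- With 240 recruited: c = 200/240 = 83.3%.
- With 80% completion: N = 200/0.80 = 250.

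Rounding 83.3% down to 80% would be unusual, and the article gives no other rate.

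**3. A possible origin.** 200 × (1 + 0.20) = 240. Multiplying by one plus the loss rate, instead of dividing by one minus it, links 200 and 240 exactly. The article does not show how 240 was derived, so this is a conjecture and nothing here depends on it.

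**4. Margin over the requirement.**
- As stated: 200 − 176 = 24 or more.
- As computed: 192 − 176 = 16.

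**5. Does 240 still cover 176?** Recruitment needed for 176 completers at 80% is 176/0.80 = 220. The target of 240 exceeds this by 20.

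**6. How the figure behaves as a minimum.** Assume, beyond what the article says, that each recruit completes independently with probability 0.80. The number completing is then binomial (240, 0.80), and:
- P(200 or more complete) ≈ 0.11;
- P(176 or more complete) ≈ 0.995.

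Under that assumption 200 would usually be missed, while 176 would almost always be met.

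**7. Effect on precision.** Interval width varies roughly with 1/√n. The ratio is √(200/192) = 1.02, so intervals would be about 2% wider at 192 than at 200.

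**The case against.** The strongest reply is that the slip changes no decision. The figure is used only to claim a modest surplus over 176, and 192 still gives one. The target of 240 stands, and precision moves by about 2%. All of this is correct, and it is why the point is minor.

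A second reply is that the analysed set is not capped at those who complete. The Data analysis section first includes participants with missing data who can be categorised, and the recruitment section says that data gathered before withdrawal will be used. Of the 240 − 192 = 48 expected non-completers, 8 (8/48 = 17%) would bring the total to 200 if they could be categorised. This stands in part: 192 is the expected number of completers, not necessarily the number analysed. It does not rescue the sentence, which derives its figure from the 80% who complete and makes no allowance for partial data.

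A reader might also infer the opposite, that exclusions will erode the 192 and use up the margin of 16. The documents do not support that. The exclusion rule concerns cases with too little information to categorise and sits beside the inclusion rule just described. Table 4 defines possible and undetermined delirium categories, but nowhere does the article say that patients placed in them are dropped. It gives no expected rate for any such loss.

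**Conclusion.** The stated analysable number is wrong as written. The article's own inputs give 192 expected completers. The overstatement is 8 patients, about 4%, and the margin over the stated 176 is 16 rather than 24 or more. This rests only on the 240 and the 80% in the text; the binomial probabilities are illustrative and the conclusion does not need them.

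A reader might go further and infer that the study is under-recruited. That does not follow from this error: at 80% completion 220 recruits would cover 176, and 240 are planned. The requirement of 176 is taken here as the article states it; whether it is the right requirement is a separate question that this point does not address. Severity is minor.

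**What to change.** In Participants and sample size, replace the stated minimum of 200 with about 192 expected completers. If the investigators really expect 200, state a completion rate of about 83% (83.3% is the exact value for 200 of 240) in place of 80%. Use the corrected figure wherever the analysable size is relied on.

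The abstract needs no change, since it gives only the recruitment total, which is consistent. The claim that the analysable number exceeds 176 can stay.

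The cost is one figure in one sentence, and a slightly smaller stated surplus. The design, eligibility criteria, procedures and recruitment target are unaffected.
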